### Procedures

A written consent is obtained by the experimenter from each participant at the beginning of the study.

#### Screening (T0)

During the first telephone contact with the interested participants, they are informed of the protocol and study design. All participants are informed about study procedures and in particular, that they will receive the intervention immediately or after 4 months, according to the group they will be assigned to. If interested, the researcher ensures that participants meet all the inclusion criteria. If eligible, two appointments for the first evaluation (T1) are scheduled.

#### Measurement points (T1, T2 and T3)

Each of these three measurement points is completed by every participant and is divided into two sessions, separated by a 9-day interval (see Fig. 1). We decided to divide into two sessions in order to minimize the burden encountered by the participants. The first session (about 2 h 30 min) is dedicated to the completion of several questionnaires and the realization of two relaxation exercises (see Table 1). During the whole session, a cardiac holter monitor is placed on participants to measure their heart rate. The second session (about 1 h 15 min) is dedicated to a computerized attentional task and to the completion of some questionnaires and open questions (see Table 1). During the 9-day interval, participants wear an actigraph (Garmin Vivoactive® HR) which measures heart rate, physical activity, and sleep. As participants do not have to do anything else with the actigraph than to recharge it, it is not considered to be complicated. The experimenter also installs an application on their smartphone (RealLife Exp, pack LifeData V5), which asks them about their emotions six times a day. In Belgium, 64% of 45–54-year-old use a smartphone, while 53% of people aged of 55 or more use one [64]. We conclude, therefore that it is likely that most of our participants are able to use a smartphone. However, a smartphone is lent to those who don’t have one and explanations are given if necessary. The experimenter also remains available by phone or email between the sessions to answer any question. Some questionnaires for partners are also given to the participants who have one with instructions to ask their spouse to complete them in order to collect data about partners’ well-being. Consent forms for partners are attached to these questionnaires. At the end of the first measurement point, participants are informed of the result of the randomization and their allocation in either the intervention group or the waiting-list control group.

**Table 1 Tab1:** Patients’ measures used in the study

T0 Screening	T1, T2 and T3 Measurement points	T4 Measurement point
*Questionnaires:*	Session 1	*Questionnaires:*
- ESAS (only 6 items)	*Questionnaires* - General information - VAS (psychological state) - ESAS (complete version) - HADS - PSWQ - FCRI - MAC - WBSI - MFI-20 - CERQ - ICQ - ISI	- MFI-20 - HADS - ESAS (complete version) - FCRI - Long-term benefits of the intervention
	*Tasks*	
	- Self-relaxation task + Questionnaire about relaxation strategies - Guided relaxation task + Questionnaire about relaxation habits	
	Between session 1 and session 2 (during 9 days) - Smartphone application (RealLifeExp) to collect information about daily emotional regulation. - Actigraph to measure sleep, activity and heart rate.	
	Session 2	
	*Questionnaires*	
	- VAS (motivation and implication) - Attentional bias task - FACT-Cog - FFMQ - MCQ-30 - PTGI - Rosenberg’s self-esteem scale - CICS - DCI - Expected/perceived benefits from the intervention	

*Abbreviations*: *VAS* Visual Analogue Scales, *ESAS* Edmonton Symptom Assessment Scale, *HADS* Hospital Anxiety and Depression Scale, *PSWQ* Penn State Worry Questionnaire, *FCRI* Fear of Cancer Recurrence Inventory, *MAC* Mental Adjustment to Cancer Scale, *WBSI* White Bear Suppression Inventory, *MFI-20* Multidimensional Fatigue Inventory, *CERQ* Cognitive Emotion Regulation Questionnaire, *ICQ* Impact of Cancer Questionnaire, *ISI* Insomnia Severity Index, *FACT-Cog* Functional Assessment of Cancer Therapy – Cognitive Function, *FFMQ* Five Facets Mindfulness Questionnaire, *MCQ-30* Metacognition Questionnaire, *PTGI* Post-Traumatic Growth Inventory, *CICS* Couples’ Illness Communication Scale, *DCI*, Dyadic Coping Inventory

#### One-year follow-up (T4)

One year after having participated in the intervention, each patient is contacted by the researcher to schedule a final group session with the therapist in order to evaluate the long-term benefits of the intervention. They discuss the application of learned skills in their daily life, perform one hypnosis exercise, and participants also have to complete some questionnaires (see Table 1). We expect the follow-up participation rate to be high, as most patient really appreciate the group session.

At each measurement point, the risk of missing responses is very low, as patients complete the scales in the presence of the investigator, who check every questionnaire after completion. All data are anonymized. A code is attributed to each participant and used during the whole study. Only the researchers involved in this study have access to the final datasets.

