### Intervention

The intervention combining self-care and hypnosis includes eight weekly 2-h sessions in group of eight participants. This has been developed and is being led by one of the authors ([name]), who is an anaesthetist and an international expert in hypnosis. She introduced the use of hypnosis as an alternative for anaesthesia in surgery in our hospital in 1991, and has been the head of the continuing and palliative care unit since 2010, where she’s supported cancer patients for decades, basing her approach on self-care tasks [65]. She has led self-hypnosis and self-care groups since 2008 for chronic pain patients, and since 2013 for cancer patients.

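### The 12-month scales are collected at a therapist-led group session that includes hypnosis, and the plan does not keep form-filling apart from that session

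*Protocol article*

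**What the plan says.** **T4.** Under One-year follow-up (T4), each patient is contacted one year after taking part in order to schedule "a final group session with the therapist in order to evaluate the long-term benefits of the intervention". Patients talk about how they use the learned skills, then the sentence continues: "perform one hypnosis exercise, and participants also have to complete some questionnaires". Table 1 lists the T4 forms as "MFI-20 - HADS - ESAS (complete version) - FCRI - Long-term benefits of the intervention". All are self-report, and the MFI-20 measures fatigue, the subject of the primary goal in Objectives.

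**Who is present.** The Intervention section says of the programme: "This has been developed and is being led by one of the authors". The next paragraph of the T4 section says that, at each measurement point, "patients complete the scales in the presence of the investigator, who check every questionnaire after completion".

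**T1 to T3.** These are assessment visits: "Each of these three measurement points is completed by every participant and is divided into two sessions, separated by a 9-day interval". The content of the first visit is described as follows: "The first session (about 2 h 30 min) is dedicated to the completion of several questionnaires", together with two relaxation exercises. No therapist and no intervention group session are described at these waves.

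**Comparator and use.** Design states that the waiting-list group receives the intervention at the latest 4 months after the first group. Statistical analyses plans a separate analysis after T4, and the Discussion presents long-term assessment as a contribution of the study.

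**The concern.** T4 brings back the main ingredients of the intervention (the group, the therapist, talk about skills, a hypnosis exercise) on the occasion when the outcome is measured. If patients fill in the forms after the exercise, immediate relief could lower their fatigue and distress scores. Even if they fill them in beforehand, the company and the occasion differ from those at T1 to T3 and could colour the answers.

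In a comparison between a treated and an untreated arm measured alike, such effects would largely cancel. At T4 there is no untreated arm, so the long-term reading rests on change within treated patients, and a transient effect cannot be told apart from a lasting one. The likely direction favours the intervention. At stake is the 12-month claim.

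Attendance adds a second, smaller issue. The group session is the only route described for T4 data, and the article expects good participation because patients like that session. Those measured may therefore lean towards the satisfied.

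**Working it through.** **1. The plan's own figure.** The sample size rests on an independent-samples t-test with d = 0.7, two-sided alpha 0.05 and power 90%. The exact noncentral t calculation gives 43.87, rounded up to 44 per arm and 88 in total, with power 0.901 at 44 per arm. The stated 88 is reproduced. It does not depend on T4.

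**2. The waves side by side.**

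| | T1 to T3 | T4 |
|---|---|---|
| Occasion | Two assessment visits 9 days apart | One group session with the therapist |
| Other content | Two relaxation exercises, attentional task, 9 days of home monitoring between visits | Skills discussion, one hypnosis exercise |
| Investigator present at completion | Yes | Yes |
| Therapist | Not described | At the session; presence during form-filling not stated either way |
| Order of forms and activity | Relaxation exercises follow the MAC and ICQ | Not stated |
| Untreated arm | Design has a waiting-list control | None: T4 falls a year after each patient's own intervention |

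The last row carries the argument. A session effect at T4 applies to every patient measured, so no contrast in the plan removes it.

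**3. Illustration of size.** The documents give no figure for a session effect, so the shift is an assumption. Take a paired comparison of an earlier wave with T4, no true change, and a session shift of δ, expressed in SDs of the change score. The test statistic then follows a noncentral t distribution with n − 1 degrees of freedom and noncentrality δ√n. With n = 88, √88 = 9.381 and the two-sided 5% critical value on 87 degrees of freedom is 1.988.

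| Assumed δ | Noncentrality at n = 88 | Share of trials with p < 0.05 |
|---|---|---|
| 0 | 0 | 5% |
| 0.05 | 0.469 | 7.5% |
| 0.1 | 0.938 | 15.3% |
| 0.2 | 1.876 | 45.8% |
| 0.3 | 2.814 | 79.5% |

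If only 70 patients attended (also assumed), shifts of 0.2 and 0.3 would give 37.8% and 69.7%.

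If the shift is expressed in SDs of the raw score instead, δ is that shift divided by √(2(1 − r)), where r is the correlation between waves. At r = 0.5 the divisor is 1 and the table is unchanged. At r = 0.7 it is √0.6 = 0.775, so a given raw shift counts for more.

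**The case against.** **Order.** A reader might infer that the hypnosis exercise precedes the forms because the sentence mentions it first. The text does not support that: its wording adds the questionnaires to the list without setting a sequence, and running order is a detail that an article may leave to the full protocol. If the forms come first, the immediate-relief part falls away. The difference in setting remains.

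**Who is in the room.** A reader might infer that the therapist replaces the experimenter as the person collecting data at T4. The statement about the investigator covers every measurement point, and Table 1 labels T4 as one. The therapist's presence during completion is implied at most. Part of the remedy may already be practice, though the text does not say that the therapist is absent.

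**Non-attenders.** A reader might infer that patients who miss the session go unmeasured. The article says that each patient is contacted and is silent on those who do not come. The limitations in the Discussion already concede that completers may be the motivated and compliant ones.

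**Earlier waves.** T1 to T3 are not neutral either. Their first session has relaxation exercises, with anxiety deliberately triggered by the MAC and the ICQ, and Table 1 lists the MFI-20 between those two. State effects there could also move the T1 to T4 difference, so a session shift need not simply add to it. In the randomised T1 to T3 comparison these tasks apply to both arms alike; at T4 there is no such balance.

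**Size.** How far one exercise can move these scales depends on item wording and recall period, which are in an additional file not shown. Very small shifts do little, as the 0.05 row shows. The planned analysis is a repeated-measures MANOVA in completers, and the paired test only stands in for it. Natural recovery, which Design mentions, could by itself make an uncontrolled change significant. That weakness is separate from this point.

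These objections limit how strongly the point can be put. They do not remove it: the article itself fixes the setting and content of T4 and states no separation between form-filling and the session.

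**Conclusion.** The point holds as a weakness in how the 12-month outcome is measured. T4 self-report scales are tied to a therapist-led group session with a hypnosis exercise, under conditions unlike T1 to T3 and with no untreated arm left, so a transient effect of session or setting would be read as lasting benefit.

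It reaches the T4 long-term claim only. The documents do not establish that bias will occur, and its size cannot be derived from them. The figures of about 15%, 46% and 79% are conditional on assumed shifts of 0.1, 0.2 and 0.3 SD of the change score, no true change, 88 patients measured and a simplified paired test. They show that a modest shift would be enough to matter, not that one exists. The change is worth making because it is cheap and removes an avoidable source of bias.

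**What to change.** In the T4 section, state that:

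- the MFI-20, HADS, ESAS, FCRI and long-term benefit questions are completed before the group session begins, either on arrival or in the preceding days;
- completion is under the experimenter, without the therapist present;
- the same forms are sent to patients who do not attend, and the number measured by each route is reported.

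The session itself and the list of scales stay as they are. The cost is a change of order, a line or two of text and a small effort to contact non-attenders. The fix does not supply an untreated comparator at 12 months, so the long-term result would still need to be described as uncontrolled change. Forms returned from home would also lack the on-the-spot check for missing items, which is a reason to prefer completion on arrival where possible.

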### Intervention

The intervention combining self-care and hypnosis includes eight weekly 2-h sessions in group of eight participants. This has been developed and is being led by one of the authors ([name]), who is an anaesthetist and an international expert in hypnosis. She introduced the use of hypnosis as an alternative for anaesthesia in surgery in our hospital in 1991, and has been the head of the continuing and palliative care unit since 2010, where she’s supported cancer patients for decades, basing her approach on self-care tasks [65]. She has led self-hypnosis and self-care groups since 2008 for chronic pain patients, and since 2013 for cancer patients.

The self-care approach is used to foster decision-making through the use of different tasks focused on well-being rather than on the disease itself. Participants have to complete these assigned tasks at home between sessions and keep a work-related diary to report how they managed it in their daily life. Examples of assignments are: adjusting self-expectation, reinforcing sense of self-esteem, revising self-narrative, adaptation of social roles, finding one’s own boundaries and personal needs, assertiveness, identifying situations and feeling of powerlessness, accepting that not everything is controllable, differentiating self from illness, managing ruminations, etc. These tasks illustrated with metaphors and humoristic anecdotes are given to patients in a practical and didactic way. This approach is based on self-management and patient empowerment approaches, which aim to strengthen self-esteem, assertion and self-confidence. Patients are encouraged to observe their thoughts and acts, and the different tasks proposed during and between sessions help them to detect and react to difficult situations. In this way, patients learn to adopt concrete changes aiming to respect themselves and others. They also learn to focus attention to positive things, life events that are going well, and to be grateful for “being alive”. An interactive and positive virtuous circle is constructed with patients all along sessions [47, 66]. Patients are asked to be actively involved in the process since the aim is to introduce change in their daily routines. In many ways, our strategies are similar with those developed in the cognitive-behavioural therapy (CBT) which is a “time-sensitive, structured, present-oriented psychotherapy directed toward solving current problems and teaching clients skills to modify dysfunctional thinking and behaviour” and which is “based on the cognitive model: the way that individuals perceive a situation is more closely connected to their reaction than the situation itself.” [67]. However, our intervention does not use CBT techniques such as cognitive restructuration or functional analysis by analysing a specific situation to understand its origin, but more generally to apprehend the future.

Concerning hypnosis, a large part of the first session is devoted to answering the participants’ questions and giving information about hypnosis. At the end of each session, a 15-min hypnosis exercise is conducted under the therapist’s supervision. Participants receive a CD for each exercise to encourage at-home practice, which is essential to take full advantage of hypnosis without the help of a therapist. It is attended that the practice of self-hypnosis will influence cognition and emotional regulation and therefore facilitate the completion of the assigned tasks. In this way, self-hypnosis is complementary to self-care tasks.

During the whole study duration, every participant in each group benefits from usual care, including medical care, oncological revalidation and individual psychological help if necessary. Although no adverse event has been reported in our previous studies [46, 47, 68], it could be possible that a patient feels uncomfortable during the group discussions or hypnosis exercises. In this case, they always have the possibility to stop the session or their participation in the study. The therapist or the experimenter can also propose a meeting to discuss their difficulties and, if necessary suggest a meeting with a psychologist or another health professional. Any reason for drop-out will be consigned.

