## Methods and design

### Design

Figure 1 illustrates the longitudinal randomized waiting-list controlled trial design used in our study. Ethics approval has been obtained from the Comité d’Ethique Hospitalo-Facultaire Universitaire de Liège. The waiting-list control design allows every participant to benefit from the intervention, which will make it possible to recruit more patients than in a no-treatment control design. It also controls the influence of natural recovery from cancer treatments and spontaneous improvement or deterioration of symptoms [59]. Each intervention will start when 16 patients have successfully completed the screening and the first measurement time (T1). Those patients will be randomized into two groups of eight participants: the first group will receive immediate intervention (intervention group) and; the second group will receive it (at the latest) 4 months later (waiting-list control group).

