### Recruitment

Participants will be recruited over a 2-year period at the University Hospital of Liège (Belgium). Potentially eligible participants are identified in several ways. First, healthcare professionals working with cancer patients (mostly oncologists, radiotherapists, psychologists, and nurses) are informed of the study and asked to talk about it to their non-metastatic patients who have finished their treatment. Interested patients should directly report to the experimenter or are advised to contact us by phone. Second, flyers and posters are displayed in different strategic areas in the hospital (mostly in oncology, radiotherapy, and algology services’ waiting rooms), which allow other health professionals and patients to be informed about the study and to contact us to participate or to talk about the study. Finally, in collaboration with the social nurse, all eligible patients are directly met after their last radiotherapy session, and are offered to participate in the study. Review of the trial process and difficulties encountered are discussed once a month between the researchers. This permitted to improve our recruitment strategies.

The recruitment started in December 2016 and is ongoing. Sample size has been determined by a power analysis in order to detect a difference in the evolution of data between the two groups. The sample size calculation was based on an independent samples t-test for a difference in mean scores. Alpha was set at 0.05, power at 90% and the standardized effect size at 0.7. The Cohen’s *d* of 0.7 is considered to be a medium to high effect size. Psycho-oncology studies which aim to assess the effect of an intervention on the patients’ quality of life often use effect sizes between 0.6 and 0.8 to calculate the sample size [62, 63]. According to this analysis, 44 patients are required in each group for a total of 88 patients.

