### Statistical analyses

Baseline (T1) demographic, medical, and psychological data will be compared between groups to test for initial groups equivalency using inferential statistics, including analyses of variance (ANOVA) and chi-square tests. Group-by time changes, and pre- and post-assessment comparison of each variable within each group will be assessed using repeated measures MANOVA, on the participant who completed all the needed assessments times. The link between a decrease in distress and attentional bias will be assessed by correlations. Correlations will also be used to assess the links between the data from the patients and their partners, and we will measure the evolution of the partners using repeated measures MANOVA. All tests will be two-tailed, and the alpha will be set at 0.05. Statistical analyses will be performed after T3 and after T4.

All participants will be informed by e-mail about the final results of the study. Scientific publications will also be planned.

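### Treatment is delivered in interactive groups of eight, but the sample size and the analysis treat patients as independent; any within-group correlation would make the test anticonservative and take a valid test below the stated 90% power.

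*Protocol article*

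**What the plan says.** Under Design, a round starts once 16 patients have been screened and have completed T1. "Those patients will be randomized into two groups of eight participants", one treated at once and one placed on a waiting list and treated within four months. Under Intervention, the treatment "includes eight weekly 2-h sessions in group of eight participants", which is 16 hours of shared contact. The same section describes an interactive process built up with patients over the sessions and mentions group discussions. One therapist leads the intervention.

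Under Recruitment, "The sample size calculation was based on an independent samples t-test for a difference in mean scores", and "Alpha was set at 0.05, power at 90% and the standardized effect size at 0.7". The result: "According to this analysis, 44 patients are required in each group for a total of 88 patients". No ICC, design effect or other inflation is given.

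Under Statistical analyses, "Group-by time changes, and pre- and post-assessment comparison of each variable within each group" are to be tested by repeated-measures MANOVA in patients who completed the required assessments. "All tests will be two-tailed, and the alpha will be set at 0.05". No term for treatment group is named, and nowhere does the article mention correlation between patients treated together.

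**The concern.** Patients who share a course of group sessions may end up more alike than patients who do not, because of the mix of people, the discussion and how that particular course went. Until the waiting list is treated, only the intervention arm has this structure, so the design is partially nested. Repeated-measures MANOVA handles correlation within a patient over time, but it takes different patients as independent. So does the t-test behind the sample size.

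With a positive within-group correlation, the mean of the treated arm varies more than either method allows. P-values for the fatigue contrast would then be too small and confidence intervals too narrow, and an analysis that allowed for the groups would have less power than stated. With 44 treated patients there are only 44/8 = 5.5 groups of eight, so a valid analysis also has little information about variation between groups.

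**Working it through.** **Inputs from the article.** Two-sided alpha 0.05, power 90%, d = 0.7 (SD taken as 1), 44 per arm, groups of 8. **Assumed, not in the article:** ICC of 0.02, 0.05 or 0.10, with clustering in the treated arm only.

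**1. The plan's own figure.** The noncentrality is 0.7 × √(44/2) = 3.283 with 86 degrees of freedom. The noncentral t gives power 0.901 at 44 per arm and 0.894 at 43. The 44 per arm is therefore correct under independence, with no margin.

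**2. Variance of the contrast.** The design effect in the treated arm is DE = 1 + (8 − 1) × ICC. The true variance relative to the independence variance is VR = (DE + 1)/2.

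**3. Type I error of the unadjusted test.** This is 2 × [1 − Φ(1.96/√VR)].

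**4. Power from clustering alone (normal approximation).** SE = √(DE/44 + 1/44) and power = Φ(0.7/SE − 1.96). At ICC 0.05, SE = √(2.35/44) = 0.2311, 0.7/0.2311 = 3.029, and Φ(1.069) = 85.7%.

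**5. Power with degrees of freedom based on the groups.** With v1 = DE/44 on 5.5 − 1 = 4.5 df and v2 = 1/44 on 43 df, the Satterthwaite df is (v1 + v2)² / (v1²/4.5 + v2²/43). At ICC 0.05 this is 12.9, and the noncentral t gives 79.9%.

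| ICC | DE | VR | SE ratio √VR | Type I error, unadjusted | Power, clustering alone | df | Power, group-based df |
|---|---|---|---|---|---|---|---|
| 0 | 1.00 | 1.000 | 1.000 | 5.0% | 90.7% | 16.3 | 87.0% |
| 0.02 | 1.14 | 1.070 | 1.034 | 5.8% | 88.8% | 14.7 | 84.2% |
| 0.05 | 1.35 | 1.175 | 1.084 | 7.1% | 85.7% | 12.9 | 79.9% |
| 0.10 | 1.70 | 1.350 | 1.162 | 9.2% | 80.7% | 11.0 | 73.0% |

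The 90.7% in the first row is the normal approximation to the 90.1% in step 1. A simulation of 40,000 trials of the unadjusted t-test, with treated groups of 8, 8, 8, 8, 8 and 4, gave type I errors of 5.7%, 6.8% and 9.1% at the three positive ICCs, in line with the formula.

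**6. Sample size for 90% power, before any few-groups correction.** 44 × VR = 47.1, 51.7 and 59.4, so about 48, 52 and 60 per arm.

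**7. How well the group variance can be estimated.** With 5.5 groups of eight, the ANOVA estimate of the between-group variance is zero or negative when the mean-square ratio is at most 1. Its probability is that of an F variable on 4.5 and 38.5 df falling below (1 − ICC)/(1 + 7 × ICC). That threshold is 0.98/1.14 = 0.860 at ICC 0.02 and 0.95/1.35 = 0.704 at ICC 0.05, giving probabilities of about 49% and 39%.

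**The case against.** The strongest reply is that the size of the problem is unknown and may be small. A reader might infer that the standard errors are certainly too small and that 90% power is certainly not delivered. The article does not support that, because it gives no ICC and at zero the type I error is correct. Some features point to a low value: one therapist leads, so there is no therapist variance; the tasks are taught didactically and done at home; and each hypnosis exercise comes with a CD for home practice. The interactive process and group discussions point the other way. This objection stands as a limit on certainty, but it does not justify independence as an unstated assumption.

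A reader might also take 84%, 80% and 73% as the cost of clustering. They are not. The same method gives 87.0% at an ICC of zero, so about three points (90.1 − 87.0) are the price of using few degrees of freedom. The clustering-only figures must stand beside them.

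Third, both arms of a cohort of 16 share calendar and recruitment effects, which cancel in the contrast and make the unadjusted test conservative for that component. In simulation, a treated-group ICC of 0.02 with an assumed shared cohort ICC of 0.05 gave a type I error of about 5.4%, and with a cohort ICC of 0.10 about 4.9%. At 0.05 for both it was still about 6.6%. The offset is real but does not remove the problem at higher group ICCs.

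Fourth, the plan is powered for a difference in evolution over time, and the ICC of change scores may differ from that of scores after treatment. This stands; it too is unknown.

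Finally, an analysis plan that is not shown might include a group term. It would then depart from the MANOVA stated here, and it could not alter the basis of the 90% already given. The article fixes both methods, so this is not a detail left for later.

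**Conclusion.** The concern holds in conditional form. The arithmetic behind 88 is right; the independence assumption is what does not fit the design. Any positive within-group correlation, not offset by shared cohort effects, makes the primary test anticonservative. Because 44 per arm only just reaches 90%, it also takes a valid test below that figure. Clustering costs under two points of power at ICC 0.02 (90.7% to 88.8%) and ten at 0.10 (90.7% to 80.7%). The inflation of type I error is slight at 0.02 and material from about 0.05.

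These figures rest on an assumed ICC range, groups of eight, clustering in the treated arm only, and no cohort effect. Once the waiting list has also been treated, both arms may be clustered and the loss is larger: by normal approximation, power is 86.8%, 80.7% and 71.2% at the three ICCs. The point should be fixed before analysis. The documents do not show that the result will be wrong.

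**What to change.** - **Model.** For the primary fatigue contrast before the waiting list is treated, replace the repeated-measures MANOVA with a partially nested linear mixed model. Include a random effect for treatment group in the treated arm, treat waiting-list patients as singletons until they are treated, and account for the cohort of 16 because both arms share it.
- **Degrees of freedom.** Use small-sample degrees of freedom tied to the number of groups. State in advance that a group variance estimated as zero does not send the analysis back to independence; at a low ICC that estimate would occur in roughly four to five trials in ten.
- **Power.** Replace the flat 90% with the power of 88 patients over a stated ICC range, showing both the clustering-only figures and those with group-based degrees of freedom.

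No new data are needed, since treatment group and cohort are known from the design. The cost is a change of model class (a repeated-measures MANOVA has no place for a group random effect), somewhat wider intervals, and a group variance estimated from only 5 to 6 groups.
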